## Abstract

**Background:**

Cytisinicline has proven to be an effective, efficient, and safe molecule in smoking cessation. However, the established 25-day regimen could be insufficient in a high percentage of smokers, so it is necessary to study maintained therapies of this drug.

**Objective:**

This study aims to compare the efficacy of the cytisinicline regimen used in routine clinical practice versus 2 maintained regimens of 50 and 75 days, respectively. In addition, the safety and economic impact of each regime will be determined.

**Methods:**

A prospective, multicenter, open-label, controlled, parallel, phase IV clinical trial of 402 smoker patients prepared to quit smoking. The study was conducted in 10 hospitals in Spain. A control group is compared to 2 intervention groups in which the duration of the drug is increased without increasing its dose, administering half and all, respectively, of an additional marketed container that includes 100 tablets. Thus, participants will be randomized to three groups in a 1:1:1 ratio to receive cytisinicline: (1) a control group treated with cytisinicline according to the usual clinical guidelines and product information (25 days); (2) a group with a 50-day cytisinicline regimen (an additional 25 days at a dose of 1.5 mg every 12 hours), seeking to increase its efficacy while minimally impacting adherence; and (3) a group with a 75-day regimen (an additional 50 days at a dose of 1.5 mg every 12 hours), attempting to increase its efficacy, although the longer duration of the drug may threaten adherence. Efficacy in the 3 arms will be analyzed through sustained abstinence at 6 and 12 months, point abstinence rate assessed every 7 days, and abstinence rate from Day 25 to Day 50 and from Day 25 to Day 75 in the 3 study arms. (1) The variation in withdrawal and craving symptoms in the 3 groups, (2) safety through the percentage of adverse events in the 3 treatment arms, and (3) economic impact by evaluating the cost-effectiveness and cost-utility ratios of the 2 prolonged regimens versus the usual clinical cytisinicline regimen. To calculate the differences between the 3 groups for each outcome variable, a univariate analysis will be performed. Statistically significant variables will be included in a multivariate model.

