#### Analysis of Demographic and Baseline Characteristics

Demographic and baseline characteristics are summarized for each study group using descriptive statistics. For continuous variables, data on the number of observations, mean, SD, minimum and maximum, or median and IQR will be presented, depending on the fit of the variable to a normal distribution. Discrete variables will be presented with frequency and percentage. Appropriate inference tests chosen according to the nature of the variables were performed to compare these characteristics between the groups under study.

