### Efficacy Analysis

To determine the main objective of the work, the efficacy variable will be constructed as a dichotomous variable, resulting from an algorithm that will be constructed for this purpose once all the data from the study have been obtained. To study the causality between efficacy and treatment prolongation, a multivariate logistic regression will be constructed. To determine candidate variables, candidate variables will first be tested in a univariate regression. Those variables whose statistical significance has a *P* value of <.20 will become part of a multivariate model. The model that best explains causality will be determined using a measure of relative statistical model quality, the Akaike information criterion. The risk measure to be calculated is the relative risk with its 95% CI. Interim follow-up assessments will be analyzed using a survival analysis to determine the duration of abstinence after the smoking cessation date.

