## Discussion

### Principal Findings

Extended treatment regimens with cytisinicline of 50 and 75 days may be more effective than the 25-day treatment regimen currently used in clinical practice. Furthermore, the percentage of adverse effects and the economic cost should not be higher with extended treatment regimens. These expected results will confirm the current scientific evidence on this drug. For example, a multicenter observational study conducted in Spain with more than 300 patients treated with cytisinicline for 25 days shows a relapse rate of 20% in the 2 months following the end of treatment. For every point increase in craving at the end of treatment, the success rate of smoking cessation decreases by 13% at 6 months of follow-up [25]. In other words, the intensity of craving at 4 weeks is inversely correlated with the drug’s efficacy. Increasing the number of days of drug administration could correct this intense desire to smoke.

Two placebo-controlled clinical trials conducted in the United States compared a cytisinicline regimen at a dose of 3 mg every 8 hours for 6 weeks versus 12 weeks. These trials showed an increase in the number of smokers who quit smoking when the treatment regimen was extended beyond 6 weeks. Furthermore, the increased number of treatment days allowed a group of smokers who were gradually reducing their consumption to quit smoking, thus increasing the percentage of smokers who quit. In other words, there will be a group of smokers who will require a longer time to quit smoking [21,22]. No greater number of adverse events were observed with these prolonged regimens. In Europe, a clinical trial in a lung cancer screening program demonstrated that a prolonged cytisinicline regimen with doses different from those specified in the product information—an 84-day regimen—was more effective than the 40-day regimen, without a greater number of side effects [23].

As strengths, it is the first study to compare 3 different cytisinicline regimens: a standard 25-day regimen used in routine clinical practice approved in the product information versus 2 prolonged treatments of double and triple duration without modifying the dose or frequency of the same, unlike other studies that evaluate a higher dose, a different frequency of administration, or compare cytisinicline with other drugs [21-23].

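### The abstract and the Methods give conflicting, significance-driven rules for entering variables into the multivariate model, and neither rule keeps out variables measured after randomisation

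*Protocol article*

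**What the plan says.** Three places in the protocol article state how variables reach a multivariate model.

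- **Abstract, Methods.** For the differences between the three arms, "for each outcome variable, a univariate analysis will be performed. Statistically significant variables will be included in a multivariate model". The outcomes listed just before include "The variation in withdrawal and craving symptoms in the 3 groups", adverse events and abstinence over several intervals.
- **Efficacy Analysis.** The stated aim is to study the causal link between prolonging treatment and efficacy with a logistic regression. For this, "candidate variables will first be tested in a univariate regression", and those with a P "value of <.20 will become part of a multivariate model". The Akaike information criterion then selects the model.
- **Safety Analysis.** The same P<.20 entry rule is used for a model of the causal link between prolongation and absence of adverse events. This section also sets statistical significance at P<.05 for all analyses.

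Two other sections bear on what could be a candidate. Specific Outcomes Efficacy has craving and the withdrawal scale (MNWS) measured at the first in-person visit and on days 25, 50 and 75. It describes the predictors of abstinence as clinical, anthropometric, demographic and smoking-related. The textbox of efficacy and safety variables lists MNWS and craving scores at each visit, and adverse events up to day 75.

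**The concern.** In a randomised comparison, a variable measured after treatment starts may itself be changed by the regimen. Holding it constant in the model then estimates only the part of the effect that does not pass through it. That is not the effect of 50 or 75 days against 25 days, which is the primary objective.

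The issue is a practical one here because the article treats craving both as a predictor and as a probable mechanism. In Principal Findings it reports that for each extra point of craving at the end of treatment "the success rate of smoking cessation decreases by 13% at 6 months of follow-up", and suggests that more days of drug could correct the urge to smoke. The Introduction argues that 25 days does not control craving and withdrawal in some smokers. A variable with that profile is likely to pass a significance screen against efficacy.

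If it did, a regimen that works by controlling craving would look less effective than it is, and the comparison would lose power. The conflict between the two rules adds a second problem: the article does not settle which screen applies, or at which threshold.

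**Working it through.** **Step 1. The rules side by side**

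| | Abstract | Efficacy Analysis |
|---|---|---|
| What is screened | outcome variables, read literally | unnamed candidate variables |
| Tested against | difference between the 3 arms | efficacy (dependent variable of the model) |
| Threshold | statistically significant (P<.05 by the Safety Analysis definition) | P<.20 |
| Then | enter the model | enter, then Akaike criterion |
| Limited to baseline? | no | no |
| Treatment arm always kept? | not stated | not stated |

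Safety Analysis matches the right-hand column on threshold and on the absence of a baseline limit.

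**Step 2. The plan's own figures**

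The concern does not rest on a stated figure, but the illustration borrows the planned rates and sample size, so these were checked first. A 3-group chi-square test (2 df, 5%) with 30%, 45% and 50% needs 109 per arm for 80% power and has 80.7% power at 110, so the plan's 110 reproduces. Then 110 × 1.21 = 133.1, rounded up to 134, and 3 × 134 = 402. (Sample Size Determination also prints .40 beside the 45%. The contrast below uses only the outer arms.)

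**Step 3. Illustration**

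Inputs from the article: 30% in the 25-day arm, 50% in the 75-day arm, 134 per arm, 5% significance (two-sided assumed). The target unadjusted odds ratio is (0.50/0.50)/(0.30/0.70) = 2.33.

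Inputs assumed, because the article does not give them: a post-baseline score M with SD 1, lowered by d SD in the 75-day arm and by d/2 in the 50-day arm, and a slope of −0.7 in log-odds of abstinence per SD.

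Model: logit P = a + t·x − 0.7·M, with M = Z − d·x and x = 0, ½, 1 for the three arms. The constants a and t are set so that the outer arms stay at 30% and 50%. There were 600 simulated trials per setting. Results for 75 v 25 days:

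| Shift d | OR without M | OR with M | Power without | Power with | M passes between-arm P<.05 | M passes P<.20 v efficacy |
|---|---|---|---|---|---|---|
| 0 | 2.33 | 2.56 | 91% | 93% | 6% | 100% |
| 0.3 | 2.39 | 2.12 | 94% | 80% | 58% | 100% |
| 0.5 | 2.31 | 1.78 | 93% | 56% | 96% | 100% |
| 0.8 | 2.37 | 1.48 | 95% | 32% | 100% | 100% |

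**Step 4. Hand check**

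With the arm rates fixed, the adjusted odds ratio should be close to 2.56 × exp(−0.7d). For d = 0.3, 0.5 and 0.8 this gives 2.08, 1.80 and 1.46, in line with the simulated 2.12, 1.78 and 1.48. The row d = 0 shows that the loss comes from the treatment-induced shift and not from adjustment as such. There the odds ratio rises slightly, as it does when a logistic model is adjusted for a prognostic variable unaffected by treatment.

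**Step 5. A milder slope**

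The only slope the article hints at is the 13% per craving point. At an abstinence rate of 35% (assumed), a risk ratio of 0.87 gives 0.3045, and (0.3045/0.6955)/(0.35/0.65) = 0.81 as an odds ratio per point. With an odds ratio of 0.80 per point, 110 per arm and an assumed fall of 0.5 or 1 point on the 0-4 scale, the odds ratio drops from 2.3-2.4 to about 2.1 or just under 2.0. Power drops from about 85% to about 75% or just under 60%. The 13% concerns craving at the end of a 25-day course in an observational study, so carrying it to day 75 is a further assumption.

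**The case against.** The strongest reply is that the abstract is condensed text and the Methods govern. Read together with Efficacy Analysis, the abstract's two sentences may mean only that, for each outcome, explanatory variables significant in univariate analysis go into that outcome's model. The predictors named under Specific Outcomes Efficacy are mainly of baseline type. The visit calendar records sociodemographic, anthropometric, diagnostic, motivation, reward and spirometry data at the first visit only. No section names on-treatment craving, MNWS, adherence or adverse events as a covariate. A full candidate list is normally left to the analysis plan, which is not shown. The craving shift and the slope used above have no source in the article.

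Most of this stands. A reader might infer from the abstract that the plan will put into the model anything that differs significantly between arms, outcomes included. The documents do not support that: the Methods screen candidates against efficacy, not between arms, and do not present outcomes as covariates. A reader might also take the simulated losses as the bias of the planned analysis. They are not, since they describe an adjustment that the article permits but does not propose.

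Two things survive. The article does state entry rules, and they disagree on what is screened, against what and at which threshold, so this is not mere silence about a list. Nor does preferring the Methods rule close the gap: the P<.20 screen against efficacy admitted the treatment-affected variable in every simulated trial, at least as often as the between-arm screen did.

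**Conclusion.** The point holds as an unresolved conflict and an open risk. The article gives two incompatible significance-driven entry rules for the multivariate model. Neither of them, nor the P<.20 rule for safety, excludes variables measured after randomisation. Followed as written, they can condition a model meant to show the causal effect of prolongation on variables that prolongation changes.

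The size cannot be fixed from the documents. Under the assumptions shown, an odds ratio of about 2.3-2.4 falls to about 2.1-1.5, and power from 93-95% to 80-32% at 134 per arm. The slope nearest to the article's own figure puts the loss at the mild end of that range. There is no attenuation if the regimen does not alter the variable. No sample-size figure changes.

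**What to change.** 1. Delete the abstract's last sentence on the multivariate model, or reword it to match Efficacy Analysis, so that one entry rule with one threshold remains.
2. State in Efficacy Analysis and in Safety Analysis that any model estimating the effect of the regimen always keeps treatment arm, whatever its P value or the Akaike criterion, and uses only covariates measured at or before randomisation.
3. State that craving, MNWS, adherence, adverse events and smoking status recorded after randomisation are not covariates in those models. Report them in separate predictor or mediator analyses, labelled as such.

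The cost is wording only: no extra patients, visits or data, and the planned predictor analyses remain possible. The change should be made before any outcome data are examined.

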**Results:**

Recruitment for the trial and patient enrollment were completed in November 2026. Follow-up of all participants will extend to December 2027.

**Conclusions:**

In conclusion, this study evaluates the optimization of cytisinicline in daily clinical practice, increasing the benefits of its pharmaceutical properties without affecting patient safety. All of this will improve the effectiveness of smoking cessation by reducing the number of smokers, which implies lower morbidity and mortality and lower costs associated with smoking.

**Trial Registration:**

European Clinical Trials Register 2024-518936-36-00; https://euclinicaltrials.eu/ctis-public/view/2024-518936-36-00

**International Registered Report Identifier (IRRID):**

PRR1-10.2196/76815

## Introduction

### Background

Cytisine (natural alkaloid), also called cytisinicline (marketed form), is extracted from a golden rain tree (*Cytisus Laburnum*) and has adverse effects similar to those reported for nicotine [1,2]. It is a partial agonist of the α4 β2 nicotinic receptors, which, when stimulated, lead to a moderate release of dopamine, contributing to the control of withdrawal symptoms. On the other hand, its antagonistic action blocks the receptor, preventing nicotine from binding to it, thus reducing the reward produced by smoking [1-4]. This duality makes cytisinicline a drug of choice for the treatment of smoking. Current scientific evidence has shown it to be a safe and effective smoking cessation molecule [5].

According to the data sheet [6] the adverse effects attributable to the use of cytisinicline, at standard doses, are mild and infrequent (<20%), with the most frequent (<20%) being gastrointestinal, dry mouth, nausea, dyspepsia, and abdominal pain. Cytisinicline is marketed as an over-the-counter drug in other European countries such as Poland, where it has been used by more than 7 million smokers, and pharmacovigilance data over the more than 50 years it has been on the market have not identified any serious or life-threatening adverse effects in smokers [7-17].

West et al [10] demonstrated that cytisinicline triples the chances of smoking cessation, and in 2 meta-analyses [11,12], where more than 4000 individuals were studied, a relative risk of 1.59 (95% CI 1.43-1.75) and 1.74 (95% CI 1.38-2.19) was found compared to placebo. These data are corroborated by new meta-analyses and systematic reviews [13-15].

In trials where it was compared with other drugs, cytisinicline demonstrated greater efficacy, measured in time to first relapse, compared with nicotine patch monotherapy [18]. Courtney et al [19], in a noninferiority trial, demonstrated that point abstinence at 4 weeks was 42.5% in the cytisinicline group vs 32.3% for varenicline, although noninferiority of cytisinicline vs varenicline could not be demonstrated at 6 months.

In Spain, cytisinicline is introduced as a smoking cessation drug in 2022 and starts to be funded by the National Health System in early 2023. The drug has demonstrated a high level of patient satisfaction and tolerability [20].

In addition, several authors have proposed various strategies to increase the efficacy/effectiveness of cytisinicline without increasing adverse effects. Rigotti et al [21], in a randomized, double-blind, placebo-controlled trial involving 810 smokers, compared 2 different durations of cytisinicline (6 or 12 weeks) versus placebo, with follow-up up to 24 weeks. For the 6-week course of cytisinicline, continuous abstinence rates were 25.3% vs 4.4% during Weeks 3-6 (odds ratio [OR] 8, 95% CI 3.9-16.3; *P*<.001) and 8.9% vs 2.6% during Weeks 3-24 (OR 3.7, 95% CI 1.5-10.2; *P*=.002). For the 12-week course of cytisinicline, continuous abstinence rates were 32.6% vs 7% during weeks 9-12 (OR 6.3, 95% CI 3.7-11.6; *P*<.001) and 21.1% vs 4.8% during weeks 9-24 (OR 5.3, 95% CI 2.8-11.1; *P*<.001). Nausea, abnormal dreams, and insomnia occurred in less than 10% of each group. Sixteen participants (2.9%) discontinued cytisinicline due to an adverse event [21,22]. The Smoking cessation with cytisinicline (SMILE) clinical trial [23] was conducted in patients in a lung cancer screening program. The study aimed to compare a 40-day cytisinicline program with an 84-day program. However, the study did not reach an adequate sample size to demonstrate a significant benefit associated with prolonged treatment. However, the data showed that the adjusted OR of 12-month continuous abstinence between standard and prolonged treatment was higher with prolonged treatment: OR 1.5 (95% CI 1-2.3).

Another clinical trial evaluated maintenance therapy with cytisinicline (cytisinicline at a standard dose for 25 days plus two 1.5 mg tablets per day for maintenance from day 26 until 12 weeks of treatment) versus varenicline at a standard dose for 12 weeks, with no difference at 6 months follow-up [24]. That is, a prolonged 3-month course of cytisinicline could be as effective as other smoking cessation drugs such as varenicline without being associated with adverse effects.

In many countries, cytisinicline is prescribed as a single 25-day course. Studies to date show that the current 25-day cytisinicline regimen is better tolerated and has fewer side effects [20]. However, there is a patient profile in whom this 25-day cytisinicline regimen is not sufficient to control cravings and withdrawal symptoms, increasing the likelihood of relapse, reducing the chances of quitting smoking, and discouraging these smokers from making another serious quit attempt with an effective drug. Recent data from Spain on experience in routine clinical practice with a 25-day cytisinicline regimen show a high rate of relapse after completing treatment. Twenty percent of smokers treated with cytisinicline at this regimen resume smoking from the end of treatment until 2 months after follow-up [25]. Establishing an optimization strategy based on prolonging treatment could increase the drug’s efficacy without being associated with a greater number of side effects, generating a favorable economic impact by increasing the number of smokers who permanently quit. We hypothesize that there is a correlation between increasing the duration of cytisinicline and its efficacy, without being associated with a greater number of adverse events/side effects.

Therefore, we aim to compare the efficacy, safety, and economic impact of this treatment regimen used in routine clinical practice in Spain versus 2 proposed extended treatment regimens (double and triple duration). Different drugs are not compared, but rather 3 different treatment regimens (25, 50, and 75 days) of the same drug (cytisinicline), one of which is the treatment regimen used in daily clinical practice.

### Objectives

The overall objective of this study is to evaluate the efficacy, safety, and economic impact of 2 extended cytisinicline regimens (50 and 75 days duration) and compare them with the standard regimen (25 days).

The primary objective is to determine the efficacy of the maintained cytisinicline regimens (50 and 75 days) versus the standard 25-day regimen.

The secondary objectives are (1) to determine the percentage and number of adverse effects in each of the 3 treatment arms and (2) to analyze the economic impact of the maintained regimens versus the standard regimen in terms of cost-effectiveness and cost-utility.

## Methods

### Trial Design

Phase IV randomized, open-label, controlled, parallel, multicenter clinical trial in patients who are candidates for smoking cessation to demonstrate the superiority of maintenance therapy with cytisinicline compared to the standard regimen.

The trial was designed according to the standardized guide for interventional trial protocols, SPIRIT (Standard Protocol Items: Recommendations for Interventional Trials statement [Multimedia Appendix 2]). A total of 402 patients from 10 smoking cessation units in Spain will be randomized. Recruitment will last for one year, with a follow-up of 52 weeks per patient recruited. Candidate patients who sign the informed consent form will be randomized to 3 possible arms in a ratio of 1:1:1.

Arm A: control group. Participants randomized to this group will be treated with cytisinicline as stated in the data sheet. They must remain smoke-free from day 5 of treatment.

Arm B: maintained therapy 1. Following the standard regimen, these patients will maintain treatment for an additional 25 days at a dose of 1.5 mg twice daily.

Arm C: maintained therapy 2. Following the standard regimen, these patients will maintain treatment for an additional 50 days at a dose of 1.5 mg twice daily (see Table 1).

At the end of the treatments, participants will continue in the follow-up phase, without treatment, until completing 52 weeks in the study (see Figure 1).

**Table 1 table1:** Dosage guidelines in each of the 3 treatment arms.

Days of treatment		Recommended dosage	Maximum daily dose	Recommendations	
